#### Trajectories

We will use GBTM to explore daily longitudinal adherence data for different adherence patterns over time. We will specify several models with the best fit using 3, 4, 5, and 6 group solutions, based on quadratic trajectories and a normal probability distribution. We will compare the models to identify the model and number of groups that best fit the data based on the lowest Bayesian information criterion (BIC) and group percentages that are sufficiently large (eg, >5% of the population). These trajectory groups will be used to assess qualitative trends in medication use that may merit further study.

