### Participants – Inclusion and Exclusion Criteria

Participants will include 40 children aged 2 to 13 years and their parent or legal guardian. To be enrolled in the study, children and their parent or legal guardian must meet the following eligibility criteria: (1) they must be receiving care for asthma on the ED or inpatient asthma pathways; (2) they must have been prescribed a daily ICS or combined ICS or long-acting beta agonist (LABA) in the year prior to the current admission and the ICS prescribed on discharge must be an MDI compatible with the electronic monitoring sensor (compatible ICS and ICS or LABA medications include Flovent [fluticasone], QVAR [budesonide], Advair MDI [fluticasone-salmeterol], Dulera [mometasone-formoterol], and Asmanex [mometasone-furoate]); (3) children and families must live or receive primary care in Philadelphia ZIP codes with the highest child asthma morbidity (greater than 100 pediatric asthma hospitalizations per year, according to Pennsylvania Health Care Cost Containment Council [22] hospitalization data); and (4) the parent or legal guardian must have a mobile phone plan with unlimited text messages.

Children will be excluded from the study if they are prescribed a controller inhaler to which the electronic device cannot affix (eg, any dry powder inhaler, Symbicort [budesonide or formoterol], or Seretide [fluticasone-salmeterol]) as their primary controller medication. Children with comorbid conditions that may influence the treatment of asthma (such as chronic lung disease, structural heart disease, or cystic fibrosis) will be excluded. Families will be excluded from the study if they have active state social services involvement or if they are non-English speaking. Subjects with significant developmental delays will also be ineligible.

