#### Adherence Trajectories

Finally, we will perform an exploratory analysis to assess for discrete trajectories of adherence using group-based trajectory modeling (GBTM). This analysis will include data from both the intervention and follow-up phases of the study. If no significant differences exist in limited efficacy outcomes between the intervention and control groups, data from both groups will be combined to produce pooled trajectory outcomes.

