#### Follow-up Phase

The follow-up phase begins the day the first follow-up call is completed and continues until 60 days following the start of the randomized intervention. The follow-up phase lasts up to 30 days. Participants will be given 2 weeks following the end of the follow-up period to complete the second follow-up call.

At 60 days, medication adherence monitoring and optional text message reminders will cease and families will receive a message from the study team to set up a second follow-up call (the study completion call) within the next few days. If the participants don’t call within 2-4 days, the research team will contact them. The second follow-up call includes a 10-minute survey for all participants. Participants will be asked again whether they have run out of ICS medication or if they had any problems using the electronic sensor and responses will be recorded. Participants initially assigned to the control group who elected to receive text messages during the follow-up phase will also complete the acceptability and preferences questionnaire.

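### The trajectory search covers only 3 to 6 groups, so an analysis meant to look for discrete adherence patterns cannot return one group or two

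*Protocol article*

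**What the plan says.** Under Outcome Measures, Adherence Trajectories, the protocol article plans an "exploratory analysis to assess for discrete trajectories of adherence" by group-based trajectory modelling, using data from both study phases. If the limited efficacy outcomes do not differ significantly between arms, "data from both groups will be combined to produce pooled trajectory outcomes".

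Under Data Analysis, Trajectories, the models are fitted to daily adherence "using 3, 4, 5, and 6 group solutions, based on quadratic trajectories and a normal probability distribution". The chosen model is the one that "best fit the data based on the lowest Bayesian information criterion (BIC") and has "group percentages that are sufficiently large (eg, >5% of the population"). The groups are then used to pick out qualitative trends for further study.

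On sample size, "Participants will include 40 children aged 2 to 13 years and their parent or legal guardian". Monitoring "continues until 60 days following the start of the randomized intervention", so each child can give up to 60 daily values. Under Limited Efficacy, adherence is defined as observed relative to prescribed actuations. The Limitations section says the study is not powered for adherence trajectories.

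**The concern.** Looking for discrete trajectories is an open question only if the answer can be that there are none. BIC compares only the models it is given. With three groups as the smallest candidate, it never weighs three groups against two or one. The number of groups reported then depends partly on where the search starts.

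Two lesser features sit beside this. Daily adherence is a ratio of puff counts that takes few values and cannot fall below zero, which a plain normal distribution describes poorly. The example size threshold is also small when only 40 children are analysed.

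At stake is a stated secondary objective: which adherence patterns are carried forward into later work on tailoring interventions. No conclusion about the text messages depends on it.

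**Working it through.** The article gives no error rate or sample size for the trajectory analysis, so there is no figure of its own to reproduce.

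**Search range.** The aim is to look for discrete trajectories; the candidates are 3, 4, 5 and 6 groups. One and two are not in the set, so neither can be selected whatever the data show. This follows from the text and needs no simulation.

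**How often this matters.** Inputs from the article: 40 children, up to 60 days, quadratic curves, normal distribution, 3-6 groups, lowest BIC, every group above 5%. Assumptions not in the article: two dosing sessions a day (daily adherence 0, 50 or 100%), no missing days, and a common residual variance in the fitted model. Two simulations were run. Run 1 used 100 data sets for each of the first two scenarios, 100 and 200 for the continuous scenario, and subject-level BIC. Run 2 used 150 data sets per scenario, mean logit -0.5 with a mild decline (two-group case: logits -1.8 and 0.8), and BIC with n = 40 and with n = 40 x 60 = 2400.

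| Simulated truth | Planned rule (3-6 groups, >5%) | Search over 1-6 groups |
|---|---|---|
| One homogeneous population | Run 1: 3 groups in 73%, no admissible model in 27%. Run 2: 3 or more in 57%, none admissible in 43% | 1 group in 100% (run 1), 98-100% (run 2) |
| Two groups | 3 or more in 75% (run 1) and 79% (run 2; none admissible in 21%) | 2 groups in 98% (run 1), 96-100% (run 2) |
| Continuous variation, no discrete groups | Run 1: 5 or 6 groups in 97-99%. Run 2 (logit SD 1.0 or 1.5): 3-6 groups in 100% | 3 or more in 100% (run 2) |

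The 73% and 57% differ by more than simulation noise. The standard errors are sqrt(0.73 x 0.27/100) = 0.044 and sqrt(0.57 x 0.43/150) = 0.040. The difference of 0.16 has standard error sqrt(0.044² + 0.040²) = 0.060, so it is about 2.7 standard errors. The exact share therefore depends on the settings; the direction does not.

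Run 2 applied the 5% screen to the estimated group proportions. Classified by most likely group, the admitted model had a smallest group of three or fewer children in 90% - 43% = 47% of the homogeneous data sets. A screen on assigned children would be stricter and would move some of these to no admissible model.

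**Size threshold.** The smallest whole number above 5% of n is floor(0.05n) + 1. For n = 40 this is floor(2) + 1 = 3 children (7.5%). For n = 20 to 39 (arms not pooled, or sensor data missing) it is floor(1 to 1.95) + 1 = 2. Under continuous variation in run 2, the smallest group held three or fewer children in 12-29% of data sets.

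**Distribution.** For a group averaging 10% with an assumed residual SD of 30 points, a normal model puts P(Z < -10/30) = 0.37 of days below zero. With SD 20 the share is P(Z < -0.50) = 0.31, and with SD 40 it is P(Z < -0.25) = 0.40. The fit is poor across that range. Yet the same normal model found the true number of groups in 96-100% once one and two were allowed, so the simulations do not show that it inflates the count.

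**The case against.** The strongest reply is that the analysis is labelled exploratory, is declared unpowered for trajectories, and yields only qualitative trends. The Introduction also cites work showing that adherence varies widely between and within children, so a homogeneous population is unlikely and a search starting above one group has a rationale. This stands as far as severity goes. It does not explain why two groups are excluded, and lack of power concerns missing real structure, not reporting structure that is absent.

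Four stronger readings are tempting and are not supported:

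- A reader might infer that discrete trajectories will always be reported when none exist. With one homogeneous population, 27-43% of simulated data sets left no model that passed the size screen.
- A reader might blame the normal distribution for spurious groups. The results above do not show this. The article also does not say whether the normal is censored or has one common variance; a fuller document may settle that.
- A reader might take three children as a fixed lower limit, or set the 6 x 3 + 5 + 1 = 24 parameters of a six-group model (with a common variance) against 40 children. The 5% is given as an example, and the parameter ratio ignores up to 60 days per child, correlated though they are.
- A reader might expect a wider search to settle whether groups are discrete. It does not. Under continuous variation, a binomial model with 1-4 groups, at least 10% of children per group and average posterior probability of at least 0.7 still gave three or four groups in 97% (logit SD 1.0) and 100% (SD 1.5) of 60 data sets each, and never one. That is a general property of the method, not a fault of this plan alone.

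**Conclusion.** The point holds for the search range. As written, the analysis cannot return one or two groups. Where the truth is one or two groups, the planned rule mostly reports three or more, and adding the two smaller models corrects this almost completely. The exclusion follows from the text alone; the percentages rest on the assumed dosing pattern, complete data and chosen adherence levels, and should be read as orders of magnitude.

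The normal distribution is a poor description of the outcome, but the documents and the calculations do not support a claim that it multiplies groups. The 5% example calls for caution in reading small groups and is not an error. Severity is minor.

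**What to change.** In the Trajectories section:

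1. Fit one- and two-group models alongside the 3-6 group models.
2. State that one group, or no admissible multi-group model, is an allowed conclusion.
3. Model daily adherence with a distribution suited to a bounded, discrete ratio: binomial with a logit link (doses taken of doses prescribed), or censored normal.
4. Report classification quality, such as average posterior membership probability, and the number of children in each group.
5. Describe the selected groups as summaries of variation between children, not as proof of discrete classes, and read groups of two or three children with caution.

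A specific minimum share such as 10-15%, or a posterior cut-off of 0.7, is a matter of preference; whichever is used should be fixed before the data are examined.

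The cost is a few sentences of analysis wording and some extra model fits. Design, recruitment and data collection do not change. The likely consequence is fewer groups and more guarded statements about them.

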## Results

Study enrollment began in December 2015 and the intervention and follow-up phases are ongoing. Results of the data analysis are expected to be available by December 2016.

## Discussion

### Contribution to the Literature

This pilot study will evaluate the feasibility, acceptability, and limited efficacy of a text message reminder intervention to improve ICS adherence in an urban minority population of children with asthma. The study will also assess trajectories of ICS adherence in the 2 months following asthma hospitalization to explore how, when, and why ICS use decays following an acute exacerbation and how this may vary between different families.

While there is a substantial body of literature investigating the reasons for poor adherence to asthma controller medications [3-5], traditional approaches to improving adherence have demonstrated inconsistent results [14-17]. New reminder systems that leverage mobile technology have demonstrated promise in improving adherence in certain populations [18,19,35], but how these technologies and interventions may work in cohorts with the highest levels of asthma morbidity and death has not been thoroughly investigated. This study will add to the literature by providing foundational feasibility data on which components of a mobile health text-message reminder intervention are acceptable and useful and which components may need to be modified to suit the needs and constraints of high risk populations.

### Limitations

We anticipate several limitations of this study. Since the study is oriented to feasibility, the study is not powered to detect between-groups differences in adherence or adherence trajectories. Differences in actuation data, parent perception of asthma control, and medication use trajectories will be evaluated to assess trends for future efficacy testing.

Given the vulnerable nature of the patient population, researcher’s ability to contact caregivers for follow-up calls will limit both completion of the intervention and follow-up surveys and ongoing syncing. Many parents have changing work schedules that make it difficult to predict availability for follow-up calls in advance. Parents also frequently change their primary phone numbers, which limits follow-up and may affect whether they receive the text message intervention for the entire study period. We will reduce this limitation by asking participants for multiple contact numbers and recording preferred times to receive calls.

Most families in this study will go home with a new ICS prescription at discharge, however, the prescription is not always filled at the on-site pharmacy, so the sensor will not always be applied by study staff. In this circumstance, the caregiver must successfully fill the prescription at their pharmacy and correctly attach the electronic sensor themselves in order for actuation data to be available. To address this concern, research staff will conduct reminder calls in the few days following discharge. As a result of this limitation, actuation data at the front end of the intervention phase may be missing for some participants.

## Appendix

Multimedia Appendix 1 Acceptability and preferences questionnaire.

Multimedia Appendix 2 Parent child conflict survey items.

Multimedia Appendix 3 EHealth Consort checklist version 1.6.1.

## Abbreviations

BIC: Bayesian information criterion
ED: emergency department
GBTM: group-based trajectory modeling
ICS: inhaled corticosteroid
LABA: long-acting beta agonist
MDI: metered dose inhalers
SMS: short message service
WTH: Way to Health
